### Recruitment and consent

Low risk ethics approval has been granted by the Eastern Health and La Trobe University human research ethics committees (LR19/014). Individual patient consent will not be sought as the data for analysis is information routinely collected to which the clinical members of the research team would normally have access. Staff participating in the focus group will provide written informed consent.

## Intervention

The intervention is the implementation of the 5-step STAT model as described in the STAT handbook [22].

Step 1 requires data to be gathered about the demand for service over the preceding year as well as the ‘supply’ or clinic capacity. The essential demand data will be the number of people referred, the number of referrals that are rejected or withdrawn prior to being provided with an appointment, and the number of people who failed to attend.

Step 2 involves use of the data to calculate the number of new patient appointments required weekly to keep up with demand, including a buffer of 15% to allow for appointments that will be unavailable due to routine factors such as staff leave. These calculations also allow for patients who fail to attend and are rescheduled, using additional appointments.

Annual data are worked into an equation as follows:
$$ \left\{\raisebox{1ex}{$\left(x-y+z\ \right)$}\!\left/ \!\raisebox{-1ex}{$52$}\right.\right\}\times 1.15= Required\ number\ of\ appointment\ slots/ week $$
$$ x= number\ of\ referrals\ received\ \mathrm{annually} $$
$$ y= number\ of\ referrals\ rejected\ or\ withdrawn\ annually $$
$$ z= number\ of\ people\  who\  fail\ \mathrm{t}o\  attend\ and\  are\  provided\ with\ a\  new\  appointment $$

Step 3 is the reduction or elimination of the backlog of people currently waiting. Previous STAT trials have used different strategies to achieve this [22] and a multi-factor strategy will be developed in consultation with epilepsy clinic staff and key stakeholders. It will be emphasised that this is one-off, and once the waitlist is at the target level, the STAT model is designed to maintain patient flow to ensure that the waitlist does not return. The backlog reduction strategy may include: auditing the waitlist to identify whether all people referred still require the service; putting on a finite number of extra clinics; or providing brief consultations by phone or telehealth. It is anticipated that this stage will take between 3 and 6 months. The aim will be to reduce wait time to a target number of weeks, to be determined by the researchers in consultation with key stakeholders from the epilepsy clinic.

Step 4 involves setting up or modifying the neurologists’ booking diaries to match the demand calculation. For example, if the final calculation indicated that 12 new appointments would be required each week to meet average demand, then the 4 neurologists would need an average of 3 new appointment slots available in each weekly clinic.

Step 5 sees a change in process where people referred are booked straight into an appointment without being placed on a waitlist. *All* referrals will be seen promptly and triage decisions regarding priority of ongoing management will be made at the first appointment by the consulting neurologist. Making these changes will likely have a flow-on effect and adjustments to caseload management are anticipated. For example, absorbing a constant flow of new assessments may instigate a review of discharge practices and management of review appointments.

### Outcome measures

Service and patient data will be collected for all people admitted during the trial period from health service databases.

The primary outcome measure will be wait time, measured by (i) the mean number of days waited from referral to first appointment for patients seen across the entirety of the pre and post intervention periods and for each month of the trial and (ii) the number of patients on the wait list at monthly time points.

Secondary outcomes will be service measures, patient outcomes and qualitative data to evaluate staff perceptions (Table 1). Service measures will be rate of failure to attend, rate of discharge, and appointment outcome (attended and scheduled for review; attended and discharged; or failed to attend). In addition, the waiting time of the longest waiters (90th percentile and mean of top 3 waiters) will be collected monthly from the beginning of the implementation and throughout the post-implementation phase. Outcomes from the initial waitlist reduction strategy will be recorded as well as costs associated with implementation. The number of new referrals received will be tracked monthly to monitor changes in demand and provide context for interpretation of results.

**Table 1 Tab1:** Outcome measures and collection phase

	Pre	During	Post
Primary outcome			
Wait time			
Number of patients on the wait list	✓	✓	✓
Number of days waiting from referral to first appointment	✓		✓
Secondary outcomes			
Service measures			
Number of appointments delivered (new and review)	✓		✓
Outcome (booked for review, failed to attend, discharged)	✓		✓
Wait time to next first appointment and next review appointment		✓	✓
Number of days waited by the longest waiters (90th percentile and top 3)	✓	✓	✓
Outcomes from initial waitlist reduction strategy (booked for assessment or removed from waitlist)		✓	
Cost directly associated with implementation		✓	
Patient outcomes			
Hospital admissions (number and total days)	✓		✓
Emergency department presentations between referral and first appointment	✓		✓
Change in management or risk between referral and first appointment	✓		✓
Staff perception			
Staff focus group			✓

Patient outcomes for the pre and post-intervention groups will include hospital admissions (number and total admitted days) and presentations to Emergency Department between date of referral and first appointment, obtained from routinely collected hospital data. Changes to patient management that occur at the first appointment, such as changes in restrictions to driving or employment or alterations in medication, will also be collected by auditing of a random sample of 100 patient medical files (50 pre and 50 post- intervention) to provide a marker of the impact of delays in accessing care on patient care.

Staff perceptions and their experience of implementing the STAT model will be sought in a focus group that will cover topics such as: how the waitlist was reduced, what support was required to implement STAT, whether there were unexpected consequences, and whether the intervention could be replicated (Table 2). Additional qualitative data will be collected via a research activity log, detailing challenges and facilitators observed. Qualitative and quantitative outcome measures will be combined in the process evaluation.

**Table 2 Tab2:** Schedule for focus group

Topic Area	Sample Questions
• Context question and general thoughts	• Please describe the changes that were made to your service in relation to the STAT model
• Pre-intervention	• Prior to the change did you perceive waiting times to be a problem in this service, and what are your thoughts on whether there was a case for change?
• Implementation period	• How would you describe your experience during the backlog reduction and setting up the new work processes? • What worked well? • What were the barriers to implementing this change? • What support did you require to implement this model?
• Effect on work practices	• How does the model affect your workload? • Describe changes to the way you manage your patients for ongoing treatment? • Were there any unexpected pathways or consequences that occurred as a result of this change?
• Effect on patient care	• What effect has the model had on patient care?
• Overall opinion/ future directions	• Can you describe any other benefits of the new system? • Can you describe any disadvantages? • Are there things that could have been done differently to improve the implementation process? • Explain your thoughts on whether this model could be implemented in other services • Do you have any other thoughts about this model and its applicability to other services?

Focus group purpose and framework:

• A focus group will be conducted with staff involved in the intervention. The purpose of the focus group is to gain insights into the process of implementing the STAT model from the service provider perspective. Of interest are the group’s views on how the STAT model impacted their workflow, whether there were benefits or drawbacks, what support was required, were there unexpected consequences and whether the model should be continued in this clinic and/or applied to other clinics

Initial statements:

• Let the staff members know that they will be asked questions about their experience of the STAT model

• Remind them that their answers will be recorded so that the researchers can review them later

### Data analysis

Primary and secondary data from the pre and post-intervention cohorts will be compared using *t*-tests for continuous data (waiting time, number of appointments, scheduled appointments, missed appointments, emergency department presentation and hospital admission data, and changes in patient risk and/or management) or equivalent non-parametric tests as appropriate. Chi squared statistics will be used to compare nominal patient-level data for the two groups.

The mean number of days waited each month and number of people on the waiting list at sequential time points will be analysed using interrupted time series regression, following methods described by Bernal [23]. It is hypothesized that the intervention will show a 40% reduction in wait time and the impact model will be a level change (Fig. 2).

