## Methods

### Design and setting

This is a pre-post study with process evaluation. Routine service data will be collected for a 12-month period prior to the intervention (retrospective data) and for 6 months after the intervention (prospective data). A six-month period is planned for implementation, but the post-implementation period will commence sooner if the existing waiting list has been reduced to below a target threshold (Fig. 1).

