### Participants

The participants are people who have been referred to the epilepsy clinic and who received their first appointment during the 12 month period prior to implementation (pre-intervention cohort) or during the 6 months following implementation of the STAT model (post-implementation cohort). In addition, the number of patients on the waiting list (referred but not allocated an appointment) will be tracked monthly from the beginning of the implementation period to the end of the post-implementation period.

Clinic staff, including neurologists, administrative staff and management, will be invited to participate in a focus group where data will be collected for evaluation of process.

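### Appointment and missed-appointment counts are compared between a 12-month and a 6-month cohort with no common time base, so per-patient review counts or period totals would about halve with no STAT effect

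*Protocol article*

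**What the plan says.** The article fixes four things that bear on this point.

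- **Periods.** Under Design and setting: "Routine service data will be collected for a 12-month period prior to the intervention (retrospective data) and for 6 months after the intervention (prospective data".
- **Cohorts.** Under Participants, the people compared are those "who received their first appointment during the 12 month period prior to implementation (pre-intervention cohort) or during the 6 months following implementation" of STAT.
- **Measures.** The Outcome measures text states: "Service measures will be rate of failure to attend, rate of discharge, and appointment outcome". The last of these is a category: attended with a review booked, attended and discharged, or did not attend. Table 1 adds a count of appointments delivered, new and review together. That count and the appointment outcome are ticked for the pre and post phases and left blank for the implementation phase.
- **Analysis.** Under Data analysis: "Primary and secondary data from the pre and post-intervention cohorts will be compared using" t-tests or non-parametric equivalents for the continuous items, listed as "waiting time, number of appointments, scheduled appointments, missed appointments, emergency department presentation and hospital admission data" and changes in risk or management. Chi-squared tests are for nominal patient-level data.

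No unit of analysis (patient, clinic or month), time base or common follow-up is attached to the three appointment counts.

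**The concern.** A review visit, or a missed review visit, can only happen after the first appointment. Someone first seen early in the pre period has up to 12 months for such visits to build up inside that period; someone first seen early in the post period has at most 6. A comparison of the two cohorts on counts within their own periods therefore mixes any effect of STAT with the length of observation.

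Research question (ii) asks about service outcomes, and the description of Step 5 expects that "absorbing a constant flow of new assessments may instigate a review of discharge practices and management of review appointments". Review and missed-visit counts are where such a change would be looked for. If STAT changed nothing, these counts could still show fewer reviews and fewer missed visits per patient, which would read as an efficiency gain.

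**Working it through.** **The plan's own figure.** Inputs from the sample size paragraph: n = 975, mean 72 days, SD 85, 40% reduction, variability halved, two-sided alpha 0.05. The split is not stated. In proportion to 12:6 months it is 975 × 12/18 = 650 and 975 × 6/18 = 325 (assumption).

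- Difference: 0.4 × 72 = 28.8 days.
- SE = √(85²/650 + 42.5²/325) = √(11.12 + 5.56) = 4.08.
- Power = Φ(28.8/4.08 − 1.96) > 0.9999. With the SD left at 85 in both periods it is 0.9988.

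The stated power of over 0.99 is reproduced. It concerns waiting time, which ends at the first appointment, so the present point does not touch it.

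**Exposure after the first appointment.** With first appointments spread evenly over a period of T months (assumption), and counting stopped at the end of the period, mean exposure is T/2: 12/2 = 6 months pre and 6/2 = 3 months post. The blank implementation column in Table 1 supports stopping the count there. Following the pre cohort into implementation would widen the gap.

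**Per-patient counts, no STAT effect.** With r reviews per month (assumed values), mean reviews are 6r pre and 3r post. Adding the first visit gives 1 + 6r and 1 + 3r.

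| Assumed review interval | Reviews, pre v post | All appointments, pre v post | Change in all appointments |
|---|---|---|---|
| 6 months | 1.0 v 0.5 | 2.0 v 1.5 | −25% |
| 3 months | 2.0 v 1.0 | 3.0 v 2.0 | −33% |
| 2 months | 3.0 v 1.5 | 4.0 v 2.5 | −38% |

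The ratio of reviews is 0.50 whatever r is. With Poisson review counts and 650 v 325 patients, a Welch t-test on reviews rejected at 0.05 in all of 2,000 simulated trials at each rate. If a fixed share f of review visits is missed, mean missed reviews are 6rf v 3rf, again a ratio of 0.50. Missed first appointments do not depend on the window in this way.

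**Raw period totals.** At a constant 975/18 = 54.2 first appointments a month, the totals are 650 v 325, a ratio of 0.50.

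**Discharge, if accumulated per patient to the end of the period.** With constant hazard h and even entry, the proportion discharged is 1 − (1 − e^(−hT))/(hT). For assumed median times to discharge of 3, 6, 12 and 24 months this gives 66% v 46%, 46% v 28%, 28% v 16% and 16% v 8% (ratios 0.69 to 0.53). If 20% to 40% are discharged at the first visit, the ratio is 0.75 to 0.87 for medians of 6 and 12 months.

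**Versions that escape.** With no effect, a t-test on 12 v 6 monthly counts (Poisson, mean 54) rejected in 5.0% of 5,000 simulations. A chi-squared test on first-appointment outcome (30% in both cohorts) rejected in 5.2%.

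**One condition on the monthly version.** The monthly counts must cover every appointment the clinic delivers. If only cohort members' reviews are counted, the number under follow-up grows from zero in each period and averages 54.2 × 6 = 325 pre and 54.2 × 3 = 162.5 post. At one review every 3 months that is about 108 v 54 reviews a month, and the halving returns.

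**The case against.** The best defence is that the wording leaves room for unbiased readings. Two period totals cannot be put into a t-test, so replicates are needed. Months are a natural replicate, because waiting time, list size and referrals are all tracked monthly, and a monthly clinic count is not biased by window length. A journal article may also leave denominators of secondary outcomes to a fuller document.

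Part of this stands: the raw-total reading fits the named test poorly, and the bias is not certain to occur. But the monthly reading has to be brought in from outside. The article says monthly for waiting time, list size, longest waiters and referrals, and does not say it for appointment counts. It does say that cohorts of people are compared. Nor is this only a missing detail, because the article itself states the cohorts, the unequal periods, the count and the test.

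A reader might infer more than the documents support:

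- **That discharge and non-attendance must also fall after STAT.** The Outcome measures section calls both rates, without a denominator, and defines appointment outcome as a category. Read at the first appointment, these are not biased by window length. The discharge figures above describe one possible reading and rest on assumed hazards.
- **That everything in the quoted list is affected.** Waiting time ends at the first appointment, and emergency presentations and admissions are counted between referral and first appointment.
- **That the protocol predicts fewer reviews per patient.** It says only that review and discharge practice may be looked at again.
- **That a shift in the mix of new and review visits is part of this fault.** Such a shift would come from protecting new-patient slots and is a separate matter from 12 v 6 months.

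**Conclusion.** The point holds for number of appointments, scheduled appointments and missed appointments, conditionally on how they are counted. Taken per patient within each period, which is the literal reading of a comparison of cohorts, reviews and missed reviews per patient would be about half as large post-implementation under no effect, and all appointments per patient 25% to 38% lower at the assumed review intervals. The halving rests on even entry and on counting that stops at the end of each period; the percentages also rest on assumed review rates. For discharge the point holds only if discharge is accumulated to the end of the period or totalled. Only secondary outcomes are involved, but they bear directly on research question (ii), and the fault is cheap to remove.

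**What to change.** State the unit and time base for these outcomes:

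1. Compare appointments delivered and missed as counts per clinic-month (12 pre values, 6 post values), with new and review appointments separate, covering all appointments at the clinic.
2. Classify disposition (review, discharged, failed to attend) at the first appointment for every patient, and compare it by chi-squared.
3. If a per-patient count of reviews or discharges is kept, use the same fixed follow-up from first appointment in both cohorts, limited to patients whose follow-up lies inside their period.

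Items 1 and 2 change wording only and use the same routine data, though item 1 rests on 18 monthly values. Item 3 loses patients. With 90 days and even entry, those first seen in the first 9 of 12 months pre (650 × 9/12, about 488) and the first 3 of 6 months post (325 × 3/6, about 163) remain, so about half of the post cohort drops out of that one secondary analysis. The 90 days is an example; a shorter window keeps more patients but sees fewer reviews.

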**Fig. 1 Fig1:**

Data collection timeline. *Number of people on the waiting list to be collected monthly throughout implementation period and post intervention period (including at the conclusion of the final month), and as available during the pre-intervention period with some missing data anticipated. Average waiting time per month is expected to be available for all time points

A process evaluation will be completed towards the end of the post-implementation phase. It will be based on Medical Research Council’s guidance and framework, combining qualitative and quantitative data to provide information on context, implementation and mechanism of impact [21].

The setting is a first-seizure and general epilepsy clinic at a public metropolitan hospital, referred to as the ‘Epilepsy Clinic’. This specialist medical outpatient clinic runs for one afternoon each week and is staffed by four neurologists. People are referred to this clinic if they have had a first suspected seizure or have previously been diagnosed with epilepsy and require neurologist care. The clinic is funded by Medicare, the Australian universal healthcare system, with no out-of-pocket expense incurred by patients. Upon receipt of a referral, a neurologist triages and allocates each referral a priority code of 1 to 4, with 1 being the most urgent. In general, priority 1 and 2 patients are seen as per government guidelines, within 1 week and 1 month, respectively. However, those triaged as less urgent, priority 3 and 4 are placed on a waitlist and may wait for several years. Over the last 2 years there have been between 600 and 700 people waiting for appointments at any given time, suggesting that supply has been keeping up with demand, but no progress has been made into reducing the entrenched backlog of waiting patients or getting to the lowest priority patients. The longest waiters have been on the waiting list for over 7 years.

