**Fig. 3 Fig3:**
[figure not shown]
Process Evaluation. Data sources-1-Organisation’s data report, 2-Focus group with staff, 3-Research log, 4-Financial report, 5-Record of backlog reduction actions. Blue boxes are key components of process evaluation. Green boxes indicate intervention and outcomes

A sample size of *n* = 975 over the 18-month data collection period will be sufficient to detect a hypothesised reduction in waiting time of 40% with a power of over 0.99, with alpha set to 0.05, based on comparison of mean waiting time pre and post intervention using a two-tailed t-test for independent groups. This estimation is based on historical data for the participating clinic with a pre-intervention mean waiting time of 72 days (SD 85 days). The calculation also assumes a 50% reduction in variability in waiting time data, based on the results of previous STAT trials [6]. There is some uncertainty in power calculations for time series analysis [23, 27], but the proposed number of monthly observations (up to *n* = 24) is expected to be sufficient to provide moderate power given a strong intervention effect, minimal seasonal effects and even distribution of data points are expected [23, 27, 28].

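### The time-series observation count includes the implementation months, but the stated impact model is a single level change that cannot describe a 3 to 6 month backlog-clearing ramp

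*Protocol article*

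**What the plan says.** All references are to the protocol article.

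- **Data analysis:** two monthly series, mean days waited and the "number of people on the waiting list at sequential time points will be analysed using interrupted time series regression". On the form of the effect, "the impact model will be a level change". No phase-in term, transition phase or exclusion is mentioned.
- **Data analysis, sample-size paragraph:** the time-series power argument, which claims moderate power, rests on "the proposed number of monthly observations (up to *n* = 24".
- **Design and Abstract:** 12 months pre, up to 6 months implementation, 6 months post. Implementation may end early if the list falls below a target.
- **Intervention, Step 3 (backlog reduction):** "It is anticipated that this stage will take between 3 and 6 months".
- **Fig. 1 caption:** "Number of people on the waiting list to be collected monthly throughout implementation period and post intervention period". It also expects average waiting time to be available at every time point.
- **Outcome measures, text:** mean days waited is to be measured over the pre and post periods "and for each month of the trial".
- **Outcome measures, Table 1:** the list count is ticked for Pre, During and Post. Days from referral to first appointment are ticked for Pre and Post only.

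**The concern.** A single level change needs each modelled month to lie before or after one step. The implementation months are neither: the list is being run down, and people seen from the backlog may carry long waits. If the months are in the regression, as the count of 24 implies, a one-step model is mis-specified, and where they are placed affects both the fitted trend and the step. If they are left out, 24 is not the number of modelled points and the power remark rests on data that are not used. Either way one statement has to change.

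Both series are primary-outcome measures, and the Discussion relies on the time series to offset part of the weakness of an uncontrolled pre-post design. The problem biases the estimate, so more months would not cure it.

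**Working it through.** **1. The plan's own figures.**

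- Count of points: 12 + 6 + 6 = 24. Pre plus post alone is 12 + 6 = 18.
- t-test power: the pre mean is 72 days (SD 85), so a 40% cut is 28.8 days, to 43.2. The split of 975 is not stated; I assume 650 and 325, in proportion to 12 and 6 months. With the post SD halved to 42.5, SE = √(85²/650 + 42.5²/325) = 4.08, and power = Φ(28.8/4.08 − 1.96) > 0.9999. With SD 85 in both periods power is 0.9988. The stated power above 0.99 is reproduced. This test uses only the pre and post cohorts, so the implementation months do not touch it.

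**2. List count, noise-free least squares on intercept, month and step.**

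Assumptions: 650 in every pre month (the article gives 600 to 700), a linear fall to 100 by the last implementation month, then 100. The end value is assumed, because the article leaves the target to be set. The true step is 100 − 650 = −550.

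Step estimate = (difference in segment means) − (pooled within-segment slope) × (difference in mean month).

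- *Six months, coded after.* The six ramp values sum to 1,975, so the mean of months 13 to 24 is (1,975 + 600)/12 = 214.6. Difference in means: −435.4. Slope: −5,729/286 = −20.03. Mean months differ by 12. Step = −435.4 + 240.4 = −195.0, or 35% of the truth.
- *Six months, coded before.* The mean of months 1 to 18 is (7,800 + 1,975)/18 = 543.1. Difference: −443.1. Slope: −13,154/502 = −26.20. Step = −443.1 + 314.4 = −128.6, or 23%.
- *Excluded.* There is no slope within either segment, so step = −550.

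| Ramp and model | Coded before | Coded after | Excluded |
|---|---|---|---|
| 6 months, trend | −129 (23%) | −195 (35%) | −550 |
| 3 months, trend | −231 (42%) | −385 (70%) | −550 |
| 6 months, no trend | −443 (81%) | −435 (79%) | −550 |
| 3 months, no trend | −477 (87%) | −489 (89%) | −550 |

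The percentages do not depend on the assumed end value: falls to 0 and to 390 give the same ones. They depend somewhat on when in the month the count is taken. With mid-month counts the no-trend range runs from about 75 to 90%. With start-of-month counts the six-month estimates with trend are 43% (before) and 15% (after). In every trend case with a six-month ramp less than half the change is recovered, and the sign is always right.

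**3. Mean days waited, true step −28.8, six-month implementation, trend fitted.**

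Let M be the mean wait in every implementation month.

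- Coded after: (M + 43.2)/2 − 72 − 216(43.2 − M)/286.
- Coded before: 43.2 − 48 − M/3 − 432(M − 72)/502.

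| M (assumed) | Coded before | Coded after |
|---|---|---|
| 72 (unchanged) | −28.8 | +7.4 |
| 100 | −62.2 | +42.5 |
| 150 | −121.9 | +105.3 |
| 200 | −181.6 | +168.0 |

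If the mean instead falls smoothly over six months, the estimates are −6.7 (before) and −10.2 (after): attenuated, not reversed. With no trend, coding after gives −0.4, +24.6 and +49.6 at M = 100, 150 and 200. Values of M above 100 are possible but not documented. At 975/18 ≈ 54 patients a month waiting 72 days, adding 10 backlog patients at an assumed 365 days gives (54×72 + 10×365)/64 ≈ 118; adding 50 gives about 213. Excluding the months returns −28.8 throughout.

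**4. What exclusion costs in precision.**

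Trend model, independent errors with SD σ, six-month implementation: SE(step) = σ/√[S(1 − r²)], where S is the sum of squares of the step indicator and r its correlation with month.

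- 24 points, coded before: S = 4.5, 1 − r² = 502/1,150, SE = 0.71σ.
- 24 points, coded after: S = 6, 1 − r² = 286/1,150, SE = 0.82σ.
- 18 points, calendar time kept: S = 4, 1 − r² = 160.5/1,060.5, SE = 1.29σ.

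The smaller errors belong to a biased estimate, but the claim of moderate power was argued on the larger count.

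**The case against.** The article never says that implementation months are coded before or after. Its design, cohort definitions and Table 1 keep three phases apart, the figure illustrating the impact model is not available, and a level change may describe only the expected effect. Transition coding is also the kind of detail an article can leave to a fuller plan. This stands in part: the coding is an inference, and leaving the months out is not ruled out. It does not remove the conflict, because the article does state the count, and 24 can be reached only with the implementation months.

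A reader might infer that the plan would reverse the apparent effect of STAT. The document does not support that. For the list count the effect shrinks and never changes sign. For days waited, reversal requires those months to be analysed, coded after, and to have mean waits that do not fall smoothly. Table 1 shows no collection of days waited during implementation, although the Fig. 1 caption and the Outcome measures text imply every month. The backlog may also be cleared partly by auditing the list, so a surge of long-wait first appointments is not a given.

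The loss is also modest if no trend is fitted. That stands, but allowing for trend is much of what a segmented regression adds to a simple pre-post comparison.

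**Conclusion.** The point holds as an internal conflict: the observation count includes up to six implementation months, and the named impact model has no place for them. With a trend and an assumed linear fall in the list over six months, one step recovers about 23 to 35% of the true pre-to-post change. For a three-month ramp it is about 42 to 70%, and without a trend about 75 to 90%. The direction of error for the list is attenuation, which would understate STAT.

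For mean days waited, exaggeration (coded before) or reversal (coded after) is possible, but it depends on assumed waits and on an inconsistency about whether those months are analysed at all. The series are illustrative, without noise or autocorrelation, and the end list size and backlog mix are assumptions. The pre/post t-test and its stated power are not affected.

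**What to change.** - **Data analysis:** state that implementation months are plotted but excluded from both segmented regressions, with the step at the first post-implementation month and month number kept on the calendar scale. Modelling them as a phase of their own is an acceptable alternative.
- **Sample-size paragraph:** with exclusion, restate the modelled observations as 18 rather than up to 24, and revisit the claim of moderate power. For the list count 18 is a ceiling, since the Fig. 1 caption anticipates missing pre-period counts.
- **Table 1, Fig. 1 caption and Outcome measures text:** reconcile whether days waited are collected in implementation months.

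The cost is a few sentences, fewer modelled points and a less favourable power statement. No data collection has to be dropped.
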